#### Nailfold videocapillaroscopy

NVC is an established non-invasive method to assess the capillary vasculature of the digital arteries, which provides information on the structural and functional abnormalities of the capillaries. It is performed at room temperature (22 °C–23 °C) with the patient seated and resting for 15 minutes. NVC will be performed at the Fourth Internal Medicine Department at Hippokrateion Hospital using an Optilia Digital Capillaroscope. Pictures and videos of 15 seconds duration will be captured using the 200x magnification video camera from the 2nd to the 5th finger of each hand. The images will be analysed with Optipix capillaroscopy software 1.7.x on a computer. The NVC parameters to be measured are: capillary density, defined as the number of capillaries in the first row in 1mm (capillaries / mm), capillary width and length (μm), the presence of micro-bleeding, oedema, thrombi, and the presence of any abnormalities in the morphology or disorder of capillary architecture. These parameters will be determined on each nail and the average of all measurements for each patient will be calculated at the end. In addition to quantitative and qualitative parameters, a semi-quantitative score will be established to assess the severity of peripheral microangiopathy.

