## METHODS

### Study design and setting

This is a prospective, observational cohort study, that will be conducted by the Fourth Internal Medicine Department at Hippokrateion General Hospital of Thessaloniki in collaboration with the Second Medical Department of the same hospital.

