## STUDY OUTCOMES

### Primary outcomes

To determine potential differences at 3 and 6 months following treatment with JAK inhibitors compared to baseline, in the following parameters: a) 24h BP, b) arterial stiffness, c) microangiopathy of dermal capillary network, d) prothrombotic markers.

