## STATISTICAL METHODS

Data analysis will be performed using SPSS (Statistical Package for Social Sciences, SPSS Inc., Chicago, IL, USA) software, version 22. Results will be expressed as frequencies for qualitative variables, and as mean±standard deviation (m±SD) or median (interquartile range) for continuous variables. Comparisons of variables will be performed between the baseline and the follow-up visits. Comparison of frequencies will be performed by Pearson chi-square test. Comparison of differences between mean values will be performed with Student’s t-test or Mann–Whitney test. Correlations between the main continuous variables will be assessed using the parametric Pearson or the nonparametric Spearman’s Rho correlation coefficient. Linear regression and logistic regression analysis will be performed to investigate whether treatment with JAK inhibitors is associated with NVC parameters and parameters obtained from 24h ambulatory blood pressure recording after adjustment for other variables. A probability value of p≤0.05 will be considered statistically significant.

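### Nailfold outcome: averaging yes/no features over eight nails and testing frequencies by Pearson chi-square do not suit paired visits, and neither masking to visit nor the severity score is fixed

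*Protocol article*

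**What the plan says.** The protocol article describes a single cohort: "This is a prospective, observational cohort study". Under Primary outcomes the aim is "To determine potential differences at 3 and 6 months following treatment with JAK inhibitors compared to baseline", and the list of parameters ends with "c) microangiopathy of dermal capillary network, d) prothrombotic markers". Each patient is therefore compared with himself or herself, and visit (before or on treatment) is the only contrast.

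The section Nailfold videocapillaroscopy has pictures and short videos taken "from the 2nd to the 5th finger of each hand", which is eight nails. It then says: "The images will be analysed with Optipix capillaroscopy software 1.7.x on a computer". It lists three measured quantities (density, width, length) and several presence/absence features (micro-bleeding, oedema, thrombi, abnormal morphology or architecture). For the whole list it says: "These parameters will be determined on each nail and the average of all measurements for each patient will be calculated at the end". It adds that "a semi-quantitative score will be established to assess the severity of peripheral microangiopathy", with no items, grades or source. It does not say who reads the images, in what order, or whether the reader knows the visit.

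The Statistical Methods section says that comparisons are between baseline and follow-up visits, and continues: "Comparison of frequencies will be performed by Pearson chi-square test". For means it names Student's t-test or the Mann–Whitney test. No test for paired data is named.

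**The concern.** Three things about this primary outcome are left in poor shape.

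- **The patient-level variable and its test do not fit together.** A yes/no feature averaged over eight nails is a proportion per patient, not a frequency of patients. Pearson's chi-square needs one yes/no value per independent subject; here there is a proportion, and the same subjects appear at both visits.
- **Masking to visit is not stated.** Whether a nail shows oedema or disordered architecture is a judgement. With no control group, a reader who knew the visit and held a consistent expectation would shift the readings of all patients the same way, and a larger sample would not remove that.
- **The score is not specified.** Unless its items and grades are fixed first, they can be settled after follow-up images have been seen.

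At stake is whether a reported change, or a reported absence of change, in the nailfold can be believed.

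**Working it through.** The article gives no effect size, SD or power for this outcome, so there is no figure to reproduce. Inputs from the article are eight nails per patient, 30 to 50 patients, and a significance level of 0.05 (taken as two-sided, since this is not stated). All other inputs below are assumptions.

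**1. What averaging produces.** With eight nails the patient value is one of 0, 1/8, 2/8, …, 1, so one nail read differently moves it by 1/8 = 12.5 percentage points. To obtain a frequency of patients, the eight readings must be reduced to yes or no, for example present in any finger. That is a different endpoint. With a per-finger probability p and independent fingers, P(any of 8) = 1 − (1 − p)^8:

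| p (finger average) | present in any finger |
|---|---|
| 0.05 | 1 − 0.95^8 = 0.34 |
| 0.10 | 1 − 0.90^8 = 0.57 |
| 0.20 | 1 − 0.80^8 = 0.83 |

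The article does not say which is meant.

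**2. Pearson chi-square on paired yes/no data.** The test treats the two visits as separate groups and takes the variance of the difference in proportions as 2p(1 − p)/n. With within-patient correlation ρ the true variance is 2p(1 − p)(1 − ρ)/n. The effective critical value is therefore 1.96/√(1 − ρ), which is 2.77 at ρ = 0.5 and 3.58 at ρ = 0.7. A simulation with no true change, prevalence 0.4 and 40,000 replicates agrees:

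| ρ | true type I error, n=30 | n=50 |
|---|---|---|
| 0 | 4.9% | 5.4% |
| 0.5 | 0.66% | 0.64% |
| 0.7 | 0.06% | 0.08% |

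The error is on the conservative side: the test would tend to miss a real change.

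**3. A systematic reading shift.** Suppose there is no true change and the reader's knowledge of visit moves readings by b SDs of the within-patient change. The mean of the t statistic is then about b√n. At b = 0.3 this is 0.3 × √30 = 1.64, 0.3 × √40 = 1.90 and 0.3 × √50 = 2.12. False-positive rates for a paired t-test, from the noncentral t distribution:

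| b | n=30 | n=50 |
|---|---|---|
| 0.1 | 8.3% | 10.7% |
| 0.2 | 18.5% | 28.4% |
| 0.3 | 35.5% | 54.8% |

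The nominal rate is 5%. The article does not say whether any such shift would occur; the table shows only what masking protects against.

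**The case against.** The strongest reply is that this is a condensed article. Reader procedures and score definitions are often left to a full protocol or reading manual, so silence on them is not an error. That is right as far as it goes, and it rules out several stronger readings.

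- A reader might infer that the images will be read with the visit identifiable. The article does not say so. It gives no reader, order or coding, so it can be said only that masking is not stated.
- A reader might infer that the score will be built from the outcome data. The wording could equally mean that a score will be assigned to each patient, and the score is additional to density, width and length. What stands is that its items and grades do not appear.
- A reader might infer that the chi-square sentence causes reader bias. It does not; the choice of test and the reading of images are separate matters.
- The direction of any reader bias cannot be predicted. The Anticipated Benefits section allows for favourable and for adverse findings.

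On the test, the chi-square sentence is general and may have been written for dipper status, while the finger average could go to the t-test or Mann–Whitney sentence. So this is a poor fit rather than a flat contradiction. But that route does not cure it: Mann–Whitney is also a test for independent samples, and the t-test is not said to be paired. If the chi-square serves dipper status, it meets the same pairing problem there.

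**Conclusion.** The point holds in a limited form and should be fixed. The firm part rests on what is printed: presence/absence features are averaged over nails, frequencies are compared between visits of the same patients by an independent-samples test, and no paired alternative is given. At an assumed prevalence of 0.4 and within-patient correlation of 0.5 to 0.7, the chi-square works at a true level of about 0.7% down to below 0.1% instead of 5%. With no correlation it would be close to 5%, so the size of the loss depends on that assumption.

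The masking part is an improvement to the design, not a proven bias. It is worth making because visit is the only contrast, some readings are judgements, and captured images can be read masked. The false-positive range, about 8% to 36% at n=30 and 11% to 55% at n=50, is conditional on an assumed shift of 0.1 to 0.3 SD and a paired t-test; it is not a forecast. The unspecified score matters in the same conditional way: it leaves room for choice after the readings are known.

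**What to change.** 1. **Reading.** Give the stored images random codes and read them in mixed order after the last visit, masked to patient and visit. If a fuller document already provides for this, one sentence in the plan is enough. The cost is a renaming step, and readings become available later.
2. **Presence features.** Choose one patient-level definition before any follow-up image is read: either the proportion of fingers affected, compared with baseline by the Wilcoxon signed-rank test, or present in any finger, compared by McNemar's test. State that the chi-square sentence does not apply to comparisons between visits of the same patients. This costs a few lines of text.
3. **Score.** Write down its items, grades and the rule for combining nails, or cite an existing score, before follow-up images are read. This costs a short paragraph.

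None of these changes adds a visit, a procedure or a patient. Which nailfold parameter should lead is for the investigators to choose.

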#### Blood tests

Routine blood tests will be performed for the evaluation of haematological and biochemical parameters (glucose, lipid levels, renal function, uric acid), erythrocyte sedimentation rate, and C-reactive protein.

In addition, blood samples will be collected, centrifuged and frozen at −80°C. Levels of the following prothrombotic markers will be simultaneously measured with ELISA (enzyme-linked immunosorbent assay) using commercially available kits: von Willebrand Factor antigen (vWF:Ag) and activity (vWF:RCo), thrombomodulin and ADAMTS13 activity.

#### Estimation of cardiovascular risk

Cardiovascular risk calculators specifically developed for RA patients have not been proved to be superior to the general population cardiovascular risk calculators, including Framingham Risk Score^49^. In our study, the relevant algorithm from the Framingham Heart Study will be used to calculate 10-year risk of general cardiovascular disease.^50^

## STUDY OUTCOMES

### Primary outcomes

To determine potential differences at 3 and 6 months following treatment with JAK inhibitors compared to baseline, in the following parameters: a) 24h BP, b) arterial stiffness, c) microangiopathy of dermal capillary network, d) prothrombotic markers.

### Secondary Outcomes

- To determine potential differences in the haemodynamic profile and the estimated 10-year cardiovascular risk of patients with RA at 3 and 6 months post-treatment with JAK inhibitors, compared to the baseline visit.- To detect potential associations of prothrombotic markers with 24h BP, arterial stiffness and microangiopathy of the dermal capillary network.

## SAMPLE SIZE

A total of 30–50 patients will be studied.

## STATISTICAL METHODS

Data analysis will be performed using SPSS (Statistical Package for Social Sciences, SPSS Inc., Chicago, IL, USA) software, version 22. Results will be expressed as frequencies for qualitative variables, and as mean±standard deviation (m±SD) or median (interquartile range) for continuous variables. Comparisons of variables will be performed between the baseline and the follow-up visits. Comparison of frequencies will be performed by Pearson chi-square test. Comparison of differences between mean values will be performed with Student’s t-test or Mann–Whitney test. Correlations between the main continuous variables will be assessed using the parametric Pearson or the nonparametric Spearman’s Rho correlation coefficient. Linear regression and logistic regression analysis will be performed to investigate whether treatment with JAK inhibitors is associated with NVC parameters and parameters obtained from 24h ambulatory blood pressure recording after adjustment for other variables. A probability value of p≤0.05 will be considered statistically significant.

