### Study overview

RA patients eligible for treatment with JAK inhibitors who will be selected on the basis of inclusion and exclusion criteria to participate in the research protocol will undergo the following procedures, before the initiation of JAK inhibitors:
Recording of medical history and current medical treatmentAnthropometric measurements, clinical examination and assessment of disease severity with calculation of DAS28 (Disease Activity Score in 28 joints)Evaluation of functional ability and quality of life through specifically designed questionnairesOffice blood pressure recordingEstimation of 10-year cardiovascular riskVideocapillaroscopy of the nailfold capillary networkAssessment of 24h blood pressure, its day- to night-time variation and haemodynamic parameters with the Mobil-O-Graph deviceBlood sampling, centrifugation and thawing of the supernatant

All patients will be re-evaluated and the above procedures will be repeated at 3 and 6 months following the baseline visit, whilst the patients are under treatment with JAK inhibitors.

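### Visit comparisons within the same patients are assigned to independent-sample tests (Mann–Whitney, Pearson chi-square), and the t-test is not stated to be paired; unpaired p-values would be conservative and could miss real changes

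*Protocol article*

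**What the plan says.** The Study design and setting section describes a single cohort ("This is a prospective, observational cohort study") and no comparison group. Under Study overview, measurements are taken before the JAK inhibitor is started, and then: "All patients will be re-evaluated and the above procedures will be repeated at 3 and 6 months following the baseline visit". The Primary outcomes section sets the contrast: "To determine potential differences at 3 and 6 months following treatment with JAK inhibitors compared to baseline".

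The Statistical Methods section ties its tests to that contrast: "Comparisons of variables will be performed between the baseline and the follow-up visits". It then names them. For categorical variables: "Comparison of frequencies will be performed by Pearson chi-square test". For continuous variables: "Comparison of differences between mean values will be performed with Student’s t-test or Mann–Whitney test". It names no paired test. Linear and logistic regression are mentioned for adjusted associations, but nothing is said about repeated measurements on a patient. The significance rule is: "A probability value of p≤0.05 will be considered statistically significant". The Sample size section states only: "A total of 30–50 patients will be studied".

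**The concern.** Every visit comparison sets a patient's later value against the same patient's earlier value. Mann–Whitney and Pearson chi-square treat the two visits as if they came from different people. Student's t-test does so too in its two-sample form, and naming Mann–Whitney as its alternative suggests that form, because the rank counterpart of the paired t-test is the Wilcoxon signed-rank test.

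Because each patient serves as his or her own control, pairing is the main source of precision in a cohort of 30–50. An unpaired test discards it: the standard error of the change comes out too large whenever visits are positively correlated. The introduction motivates the study by a cardiovascular safety signal, and the Anticipated benefits section expects direct clinical implications. A null result produced by an insensitive test could then be read as reassurance about blood pressure, stiffness, capillaries or prothrombotic markers.

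**Working it through.** **Inputs from the article.** n = 30 to 50 patients, each measured at baseline, 3 and 6 months; significance at p ≤ 0.05 (sidedness not stated, two-sided assumed). The sample size is given without effect size, SD, correlation or power, so there is no derivation to reproduce.

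**Assumed.** Within-patient correlation ρ between two visits of 0.3, 0.5 and 0.7; equal SD at both visits; bivariate normal data for the continuous case.

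**Step 1: standard errors, with SD the SD of the raw measurement.**
- True SE of the mean change: SD·√(2(1−ρ)/n).
- SE used by an unpaired test: SD·√(2/n).
- Ratio, unpaired to true: 1/√(1−ρ) = 1.20, 1.41 and 1.83 at ρ = 0.3, 0.5 and 0.7.

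**Step 2: true type I error of the unpaired t-test at nominal 5%.** Approximately 2·[1 − Φ(1.96/√(1−ρ))]:
- ρ = 0.3: 1.96/0.837 = 2.34, giving 0.019.
- ρ = 0.5: 1.96/0.707 = 2.77, giving 0.006.
- ρ = 0.7: 1.96/0.548 = 3.58, giving 0.0003.

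Simulation with 20,000 data sets per setting gave 0.020, 0.006–0.007 and 0.0004–0.001 for the two-sample t-test. Mann–Whitney (4,000 data sets) gave 0.017–0.019, 0.007–0.009 and about 0.001. Pearson chi-square on paired binary data, at an assumed 50% prevalence and phi = 0.3, 0.5 and 0.7, gave 0.020–0.023, 0.005–0.007 and 0.001. The paired t-test stayed between 0.046 and 0.051 throughout.

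**Step 3: power of the unpaired test where the paired t-test has 80%.** By normal approximation the power is Φ(2.80 − 1.96/√(1−ρ)), with 2.80 = 1.96 + 0.84:
- ρ = 0.3: Φ(0.46) = 68%.
- ρ = 0.5: Φ(0.03) = 51%.
- ρ = 0.7: Φ(−0.78) = 22%.

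Simulation, with the effect set by the noncentral t:

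| ρ | paired t | two-sample t (n=30 / n=50) | Mann–Whitney (n=30 / n=50) |
|---|---|---|---|
| 0.3 | 80% | 69% / 69% | 66% / 66% |
| 0.5 | 80% | 54% / 53% | 50% / 50% |
| 0.7 | 80% | 25% / 23% | 23% / 23% |

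**Step 4: change detectable with 80% power, in SDs of the raw measurement (normal approximation).**
- Paired: 2.80·√(2(1−ρ)/n).
- Unpaired test on paired data: 1.96·√(2/n) + 0.84·√(2(1−ρ)/n).
- Example, n = 30 and ρ = 0.5: paired 2.80 × 0.1826 = 0.51; unpaired 1.96 × 0.2582 + 0.84 × 0.1826 = 0.506 + 0.154 = 0.66.

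| n | ρ | paired | unpaired |
|---|---|---|---|
| 30 | 0.3 | 0.61 | 0.69 |
| 30 | 0.5 | 0.51 | 0.66 |
| 30 | 0.7 | 0.40 | 0.63 |
| 50 | 0.3 | 0.47 | 0.53 |
| 50 | 0.5 | 0.40 | 0.51 |
| 50 | 0.7 | 0.31 | 0.48 |

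The usual two-sample formula (about 0.74 SD at n = 30 and 0.57 SD at n = 50) should not be used for this comparison. It describes truly independent groups, and it overstates the penalty when the data are in fact paired.

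**The case against.** **The t-test may be meant as paired.** This stands in part. The paired t-test is a Student's t-test, and the section says that the comparison is between visits. Most primary variables are continuous (24h BP, PWV, AIx, capillary measurements, ELISA markers), and any analysed by a paired t-test would have valid p-values. A reader might infer that every primary p-value will be wrong; the text does not show that. What remains certain is narrower: continuous variables sent to Mann–Whitney, and frequencies such as dipper status or the presence of capillary abnormalities sent to chi-square.

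**The loss of power rests on an unknown correlation.** This also stands. A reader might infer that most of the power is lost, but that holds only in some settings. For an assumed change of 0.4 SD and correlation 0.7, power falls from 78% to 23% at n = 30, but from 95% to 51% at n = 50. At correlation 0.5 and n = 50 it falls from 80% to 52%. At correlation 0.3 the fall from 80% is about 11 points.

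**The error is on the cautious side.** True if correlation is positive: the estimated changes are the same and false positives become rarer than nominal. In a study looking for possible harm, however, missing a real change is itself costly.

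**An analysis plan or a group comparison could account for it.** Neither answers the point. This is not a detail left open: the article names tests, and a separate plan with paired tests would contradict it. The article defines no second patient group for independent-sample tests to compare.

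**Conclusion.** The point holds in limited form. Mann–Whitney and Pearson chi-square are the wrong tests for the visit comparisons to which the article assigns them, and the t-test is left ambiguous. With positive within-patient correlation the consequence is conservative p-values and, if intervals are built the same way, confidence intervals too wide by a factor of 1.20 to 1.83 over the correlations examined. The risk is a missed change, not a spurious one.

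The size depends on a correlation that the documents do not give. The loss from 80% power is about 11 points at 0.3, about 27 at 0.5 and about 56 at 0.7, so it is severe only if correlation is high. The figures also assume two-sided testing, equal SDs and, for continuous variables, normal data. Because the stated method does not fit the stated contrast and costs nothing to correct, it should be corrected before the analysis.

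**What to change.** In the Statistical Methods section, replace the two sentences that name the tests for visit comparisons with wording such as:

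*Changes from baseline to 3 and to 6 months will be analysed within patients: by paired t-test for continuous variables, or by the Wilcoxon signed-rank test if the differences are clearly non-normal, and by McNemar's test for binary variables. Mean changes will be reported with 95% confidence intervals.*

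An equally sound alternative is one model over all three visits: a linear mixed model with visit as a fixed factor and patient as a random effect for continuous variables, and GEE for binary ones. Name one of the two approaches before the data are analysed. If the t-test was always meant to be paired, adding that word settles that part; Mann–Whitney and Pearson chi-square still need replacing for visit comparisons.

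The cost is a few sentences. No new data, visits or patients are needed, and the procedures are standard in statistical software.

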### Inclusion criteria

This study enrols adult patients with an established diagnosis of RA according to the American Rheumatism Association 1987 Revised Criteria,^45^ who are eligible for treatment with JAK inhibitors (tofacitinib, baricitinib or upadacitinib) for first time, irrespective of previous administration of conventional or biologic DMARDs based on international recommendations (EULAR 2020).^15^

Exclusion criteria include: age <18 years, inability to comprehend and sign the informed consent, previous exposure to JAK inhibitors, concomitant active malignancy or other disease with poor prognosis, recent major adverse cardiovascular event (myocardial infarction, unstable angina, stroke) within the past 6 months, and stage III–IV heart failure according to the New York Heart Association (NYHA) criteria.^46^

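### The regression on JAK inhibitor treatment has no untreated patients to compare with: its treatment term is either not estimable or is simply the before/after visit contrast

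*Protocol article*

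**What the plan says.** The design is a single cohort (Study design and setting: "This is a prospective, observational cohort study"). The inclusion criteria admit patients "who are eligible for treatment with JAK inhibitors (tofacitinib, baricitinib or upadacitinib) for first time", and previous exposure to a JAK inhibitor is an exclusion. Under Study overview, participants "will undergo the following procedures, before the initiation of JAK inhibitors", and the assessments are repeated "at 3 and 6 months following the baseline visit, whilst the patients are under treatment with JAK inhibitors". No untreated group and no group on another drug is described.

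The primary outcomes are within-patient changes: "To determine potential differences at 3 and 6 months following treatment with JAK inhibitors compared to baseline". Statistical Methods first describes comparisons between baseline and follow-up visits. It then adds a modelling step: "Linear regression and logistic regression analysis will be performed to investigate whether treatment with JAK inhibitors is associated with NVC parameters" and with parameters from the 24-hour recording, adjusted for other variables that are not named. No mixed model, GEE, clustered standard error or other repeated-measures method is mentioned for this step.

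**The concern.** A regression coefficient for treatment needs variation in treatment that is not the same thing as something else in the data. Here treatment changes only when the visit changes, and it does so for everyone at once. Whatever else moves between baseline and follow-up coincides with it: time, regression to the mean, falling disease activity, changes in other medication.

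This is the plan's only adjusted analysis. A reader would take its coefficient as an adjusted association with JAK inhibition, which a cohort without a comparator cannot supply. If ordinary regression is also run on repeated rows, a real rise in blood pressure or stiffness could be missed. That is not a harmless error in a study looking for possible cardiovascular harm.

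**Working it through.** The article gives 30 to 50 patients without an effect size, SD or power, so there is no stated figure to reproduce. The check is of structure first, then of size under assumptions.

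**1. One row per patient.** At baseline treatment = 0 for all; at 3 or 6 months treatment = 1 for all. A design matrix of intercept, treatment and one covariate has 3 columns and rank 2, at n = 30 and at n = 50. The treatment coefficient is not estimable.

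**2. Three visits per patient, stacked.** Treatment is (0, 1, 1) for every patient. Its correlation with the post-baseline indicator is 1. Intercept, treatment and two visit indicators give 4 columns and rank 3. Treatment cannot be separated from visit.

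**3. Errors if stacked rows are analysed by ordinary regression.** Assumptions: total variance 1 at each visit and equal within-patient correlation ρ, which the article does not give.

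- Baseline against one follow-up: the true variance is 2(1−ρ)/n, while ordinary regression uses about 2/n.
- Mean of both follow-ups against baseline: the true variance is 1.5(1−ρ)/n, while ordinary regression uses about 1.5/n.
- In both cases the standard error is too large by 1/√(1−ρ).
- For a covariate fixed within patient, on three rows, the true standard error is √(1+2ρ) times the one reported. A nominal 5% test then has size 2Φ(−1.96/√(1+2ρ)).

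| ρ | Visit term: SE too large by | Patient-level covariate: SE too small by | Actual size of nominal 5% covariate test |
|---|---|---|---|
| 0.3 | 1.20 | 1.26 | 12% |
| 0.5 | 1.41 | 1.41 | 17% |
| 0.7 | 1.83 | 1.55 | 21% |
| 0.8 | 2.24 | 1.61 | 22% |

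The visit test is conservative. By simulation it rejects a true null in about 2% of studies at ρ = 0.3 and in under 1% at ρ = 0.5 or more, instead of 5%.

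**4. Power.** Assumptions: n = 40, a change of 0.35 SD at both follow-ups, two-sided 5%.

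| ρ | Pooled pre/post, stacked regression (simulated) | Pooled pre/post, within patient (simulated) | One follow-up v baseline, paired |
|---|---|---|---|
| 0.5 | 42% | 72% | 58% |
| 0.7 | 38% | 89% | 80% |
| 0.8 | 39% | 98% | 93% |

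The first two columns compare like with like. A noncentral-t calculation of the second column, with standard error √(1.5(1−ρ)/40), gives 70%, 90% and 98%, so the simulated values are sound. For the third column the standard error is √(2(1−ρ)/40); at ρ = 0.7 this is 0.122, and 0.35/0.122 = 2.86, which gives 80%. Over the planned range at ρ = 0.7, the pooled contrast has 26% (stacked) against 79% (within patient) at n = 30, and 53% against 95% at n = 50.

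**5. What adjustment can do.** In the linear model with complete data, adding a covariate fixed within patient moved the treatment coefficient by less than 1e-14: it remains the raw mean change. Adjusting for on-treatment values of something the drug itself changes can remove real effect. In an extreme illustration (40 patients, a change of 0.35 acting wholly through the covariate) the adjusted change fell to about 0.01.

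**The case against.** Several points on the other side have force.

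- **Stacking is not stated.** This stands. Regressing each patient's change on centred covariates is also linear regression, and its intercept has valid errors. Stacking is the natural route to a coefficient labelled treatment, because the contrast exists only across visits, but sections 3 and 4 of the working apply only if it is done. The intercept of a change-score model is still the visit change and not a treatment coefficient, so the structural point does not depend on stacking.
- **Adjustment may be useful.** A reader might infer that the model adjusts for nothing that could bias the change. The text does not support that: it names no covariates, and medication and DAS28 are recorded again at each visit. The narrower point stands: no covariate creates a comparator.
- **Another meaning of treatment.** Type of JAK inhibitor or duration of exposure would be estimable. The article mentions neither as the term, and neither answers the question it states.
- **Prothrombotic markers.** A reader might count it as an error that primary outcome d) is outside the adjusted models. It is a choice of scope; the general comparisons between visits cover these markers.
- **The regression is additional.** The primary outcomes are addressed by the separate visit comparisons. If rows are stacked, the error on the treatment term is conservative, and the inflated error rates fall on covariates that are not the target. This limits the damage but does not rescue the stated purpose.
- **Detail belongs in a fuller plan.** The list of covariates does. A stated model whose stated purpose the design cannot serve is not an omission.

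**Conclusion.** The point holds on structure without any assumption: in this cohort the treatment term is not estimable at a single visit and is the pre/post contrast across visits, so the planned regression cannot yield an adjusted treatment association.

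The size is conditional on stacked ordinary regression, on equal within-patient correlations of 0.5 to 0.8, and on a 0.35 SD change in 40 patients, none of which the article fixes. The power loss for the pooled contrast is then from 72–98% to about 40%. The 72–98% should not be read as the power at each visit, which is about 58–93% with a paired contrast. The documents do not show that the errors will be wrong, only that nothing in the sentence protects against it. Nor do they show that the change-from-baseline outcomes are themselves ill-defined. The sentence should be corrected before analysis.

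**What to change.** Replace the regression sentence as follows.

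- For continuous outcomes, fit a linear mixed model with visit (0, 3, 6 months) as a categorical fixed effect and a random patient intercept.
- For binary features, fit a logistic GEE clustered on patient with the same visit term.
- Report the visit coefficients as change from baseline at 3 and 6 months, not as an association with treatment.
- Make the change not adjusted for on-treatment variables the main result. Show any adjustment for time-varying co-medication beside it.
- Treat adjustment for on-treatment DAS28 or CRP only as an exploratory, mediation-type analysis. The article itself describes JAK inhibitors as effective in suppressing RA inflammation, so these variables plausibly lie on the causal path.

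The cost is one paragraph of wording and standard procedures in the planned software; no new data are needed. The downside is that the result can no longer be described as an adjusted treatment association. Keeping that claim would require a comparator cohort.
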